**Methods:**

This is a prospective, randomized, double-blind, placebo-controlled, multicenter clinical trial. We plan to recruit 286 perioperative LAGC patients from multiple hospitals in China. Participants will be randomly assigned (1:1) using a central interactive web response system with allocation concealment, stratified by the use of neoadjuvant chemotherapy ± immunotherapy, to either the control group (n=143, placebo containing 5% SQFWG) or the experimental group (n=143, SQFWG). Both groups will concurrently receive perioperative treatment (chemotherapy ± immunotherapy). Follow-up assessments will be conducted every 3 months for 3 years after treatment completion or upon reaching an endpoint event. The primary efficacy endpoint is event-free survival. Secondary outcomes include overall survival, cumulative 1-/2-/3-year recurrence and metastasis rates, surgical conversion rate, quality of life, and safety. At the same time, prespecified subgroup analyses will be performed according to the use of immunotherapy and the type of chemotherapy regimen, and the clinical applicability of SQFWG will be further explored.

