#### Inclusion criteria

2.2.1

Histologically or cytologically confirmed adenocarcinoma of the stomach or gastroesophageal junction.Resectable or potentially resectable disease with a clinical stage of cT1-2bN1-3M0, cT3-4bN0M0, or cT3-4aN1-3M0 (Stage II–III).Previous anti-tumor treatment, including chemotherapy, radiotherapy, immunotherapy or targeted therapy, is not permitted;Adequate organ function, defined as:• Absolute neutrophil count ≥ 1.5 × 10^9^/L• Hemoglobin ≥ 9.0 g/dL• Platelet count ≥ 80 × 10^9^/L• Serum albumin ≥ 30 g/L• Serum total bilirubin ≤ 1.5 × upper limit of normal (ULN)• Aspartate aminotransferase and alanine aminotransferase ≤ 2.5 × ULN• Alkaline phosphatase ≤ 2.5 × ULN• Serum creatinine ≤ 1.5 × ULNKarnofsky Performance Status score ≥ 70.Age between 18 and 75 years.Willing and able to provide written informed consent.

*Potentially resectable disease is defined, as clinical stage II–III disease, according to CSCO gastric cancer guidelines and multidisciplinary team (including surgical oncologists and radiologists) assessment, including tumors considered technically unresectable at diagnosis but potentially convertible to R0 resection following neoadjuvant therapy.

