### Randomization method

2.3

The blinded document (Participant Randomization Table and Drug Assignment Table) of this trial is generated by unblinded statistician using SAS software (Version 9.4) and uploaded to the central randomization system by the randomization system administrator (provided by Beijing Bio-Thera Information Technology Co., Ltd). SAS software was used to generate random numbers and treatment groups corresponding to random numbers. Parameters such as procedure, seed number, block length during randomization were kept in an unblinded folder and the randomization table was reproducible. These persons were not involved in participant recruitment, treatment, or outcome assessment. The central randomization system will complete the assignment of participant randomization number and drug management during the trial. This trial was stratified by neoadjuvant chemotherapy ± immunotherapy using stratified block randomization. Authorized study personnel at each participating site performed subject assignment via the randomization system after confirming eligibility and obtaining informed consent. The grouping process was done automatically by a centralized system and did not rely on the subjective judgment of the researcher.

To ensure data confidentiality and prevent unauthorized access, the randomization system maintains a complete electronic audit trail documenting all allocation-related activities, including login attempts, randomization requests, data entries, and emergency unblinding, with timestamps and user identification. Access to the randomization module is strictly role-based, with different authorization levels assigned to investigators, study coordinators, statisticians, and system administrators. The integrity of the allocation process is further overseen by independent clinical monitors. The randomization schedule itself remains sealed and inaccessible to all study personnel until database lock, except for emergency unblinding.

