### Sample size calculation

2.5

This is a randomized, placebo-controlled superiority trial with a 1:1 allocation ratio. The primary endpoint is EFS. Based on the KEYNOTE-585 trial results (11), the assumed 3-year EFS rate for the control group (receiving perioperative chemotherapy ± immunotherapy) is 44%. We hypothesize that the addition of SQFWG will increase the 3-year EFS rate by 20% (absolute improvement), resulting in a rate of 64% for the experimental group. Using a two-sided significance level (α) of 0.05 and a power (1-β) of 80%, and assuming a constant accrual rate over an enrollment period of 36 months, the sample size was calculated using PASS software (version 15). This calculation yielded 114 participants per group. To account for an estimated 20% dropout rate, the final target enrollment is set at 143 participants per group. The design is event-driven, requiring a sample size of 286 cases. The duration of enrollment is 3 years, and the total study duration is 5 years, taking into account a 20% dropout rate.

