### Interventions

2.6

Experimental Group: Participants will receive SQFWG, composed of *Astragalus membranaceus* (Huangqi), *Codonopsis pilosula* (Dangshen), *Atractylodes macrocephala* (Baizhu), *Gallus domesticus* (Jineijin, endothelium corneum of chicken gizzard), stir-fried *Hordeum vulgare* (Chao Maiya), stir-fried *Setaria italica* (Chao Guya), *Glycyrrhiza uralensis* (Gancao), and other herbs in specified ratios, in addition to the perioperative therapy. The granules will be administered orally at a dose of one packet three times daily, dissolved in hot water and taken after meals. Each treatment cycle is 3 weeks, synchronized with the chemotherapy schedule. Administration will continue concurrently with perioperative therapy until disease progression, unacceptable toxicity, or completion of the prescribed therapy. For patients undergoing surgery, oral administration will resume postoperatively based on recovery status.Control Group: Participants will receive a matched placebo in addition to the perioperative therapy. The placebo is designed to be indistinguishable from the active granules in outer packaging, dosage form (color, shape), and taste. Its composition includes: SQFWG extract powder (5%, sub-therapeutic dose), maltodextrin, a bitter flavoring agent, sucralose, yellow dextrin, and brown dextrin. Maltodextrin and sucralose conform to the standards for pharmaceutical excipients as per the Chinese Pharmacopoeia (2025 Edition, Volume IV). The bitter flavoring agent, yellow dextrin, and brown dextrin are food-grade additives compliant with national food safety standards. The dosing regimen (dose, frequency, and route) is identical to that of the experimental group.Perioperative Therapy (Both Groups): Participating centers will follow unified protocol-specified perioperative treatment principles based on contemporary CSCO and international guidelines. Based on the results of the KEYNOTE-585 (11) and RESOLVE (7) trials, the primary chemotherapy regimens are limited to SOX or XELOX. The preoperative phase will consist of 2–4 cycles of neoadjuvant SOX or XELOX chemotherapy, with or without immunotherapy. Postoperatively, participants will receive 4–6 cycles of adjuvant SOX chemotherapy (which may be followed by S-1 monotherapy) or 4–6 cycles of XELOX chemotherapy, with or without immunotherapy. Treatment will continue until disease progression, unacceptable toxicity, or completion of the planned cycles. The specific immunotherapy regimen is not restricted by the protocol. Immunotherapy (e.g., pembrolizumab, durvalumab, camrelizumab, or other PD-1/PD-L1 inhibitors) is permitted only for patients with biomarker evidence of potential benefit (e.g., PD-L1 CPS ≥5, MSI-H, or EBV positivity) based on current guidelines. The choice of agent is at the investigator’s discretion, the specific agent, number of cycles, and timing must be documented, but not restricted to reflect real-world practice.① Chemotherapy regimens:SOX regimen (3-week cycle): Oxaliplatin 130 mg/m², administered intravenously over 2 hours on Day 1; S-1 40–60 mg (based on body surface area: <1.25 m²: 40 mg; 1.25–1.5 m²: 50 mg; >1.5 m²: 60 mg), taken orally twice daily after meals on Days 1–14, followed by a 7-day treatment-free interval.XELOX regimen (3-week cycle): Oxaliplatin 130 mg/m², administered intravenously over 2 hours on Day 1; Capecitabine 1,000 mg/m², taken orally twice daily on Days 1–14, followed by a 7-day treatment-free interval.② Immunotherapy regimens:Pembrolizumab: 200 mg administered intravenously over 30 minutes on Day 1 of each 3-week cycle.Durvalumab: 1,500 mg administered intravenously over 60 minutes on Day 1 of each 4-week cycle.Camrelizumab or Sintilimab: Administered per standard institutional protocols at approved doses (typically 200 mg Q3W for Camrelizumab; 200 mg Q3W for Sintilimab).The protocol specifies the recommended dosing schedules for commonly used PD-1/PD-L1 inhibitors administered according to the approved product labeling and current clinical guidelines. The duration of immunotherapy is also defined in accordance with routine perioperative treatment recommendations.③ Dose adjustment rules:Dose modifications for chemotherapy are based on the severity of adverse events per NCI-CTCAE v5.0, including hematologic toxicity, thrombocytopenia, peripheral neuropathy, hepatic dysfunction, renal impairment, and other significant adverse events. For oxaliplatin-related neurotoxicity (grade ≥2), oxaliplatin may be held or reduced by 25%; for grade ≥3, oxaliplatin is discontinued. For thrombocytopenia (platelet <75×10^9^/L), oxaliplatin is held until recovery to ≥100×10^9^/L; for grade 3–4 thrombocytopenia, the dose is reduced by 25% upon re-administration. For S-1 or capecitabine, dose adjustments are based on gastrointestinal toxicity, hand-foot syndrome, and myelosuppression, using standard dose reduction levels (100% → 75% → 50% → discontinuation).Immunotherapy dose modifications follow current international consensus guidelines and the prescribing information for each immune checkpoint inhibitor, with corticosteroid management for immune-related adverse events as per standard practice, e.g., hold for grade 2 pneumonitis/colitis; discontinue permanently for grade 3 or higher. All dose modifications will be recorded prospectively.”Concomitant Medications: Supportive care will be provided to all patients according to clinical oncology guidelines. The use of other Chinese herbal decoctions with purported similar effects, anti-tumor Chinese herbal injections, Chinese patent medicines, thymic peptides, or other immunomodulatory biological agents is prohibited during the study period. Any changes in concomitant medications will be recorded.

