#### Secondary outcomes

2.7.2

Survival Outcomes:• DFS: Time from the date of surgery to tumor recurrence, metastasis, or death from any cause.• Overall Survival (OS): Time from randomization to death from any cause.• Cumulative 1-, 2-, and 3-Year Recurrence/Metastasis Rate: The proportion of patients experiencing recurrence or metastasis at 1, 2, and 3 years from randomization.• Cumulative 1-, 2-, and 3-Year Survival Rate: The proportion of patients alive at 1, 2, and 3 years from the date of surgery.Surgical Conversion Rate: Proportion of patients who successfully undergo R0 resection following neoadjuvant therapy.Infection and Complications:• Perioperative infection rate.• Incidence of early (≤30 days) and late (≤12 months) postoperative complications.Patient-Reported Outcomes:• QoL: Assessed using the Functional Assessment of Cancer Therapy - Gastric scale.• Symptom Burden: Assessed using the Edmonton Symptom Assessment System.• TCM Symptoms: Assessed using the MD Anderson Symptom Inventory - TCM Module.Treatment Delivery Indicators:• Chemotherapy Completion Rate: Proportion of planned adjuvant chemotherapy cycles completed.• Medication Adherence: Calculated based on the number of study drug packets consumed. Adherence will be categorized as <80%, 80-120%, and >120%. The number and percentage of patients in each category will be reported.Immunological Biomarkers: Levels of circulating T cells, regulatory T cells, CD4+ T cells, and CD8+ T cells.Serum Tumor Markers: Carcinoembryonic Antigen, Carbohydrate Antigen 72-4, Carbohydrate Antigen 19-9, and Carbohydrate Antigen 125.

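### The surgical conversion rate is defined as an R0 resection rate with no restriction to tumours that needed conversion, so its name and content do not match

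*Protocol article*

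**What the plan says.** The Abstract (Methods) names the outcome among the secondary endpoints: "cumulative 1-/2-/3-year recurrence and metastasis rates, surgical conversion rate, quality of life, and safety". Section 2.7.2 gives its one-line definition: "Proportion of patients who successfully undergo R0 resection following neoadjuvant therapy".

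The entry criteria in section 2.2.1 admit a mixed population: "Resectable or potentially resectable disease with a clinical stage of" the listed categories. The footnote there describes potentially resectable disease as stage II–III disease, "including tumors considered technically unresectable at diagnosis but potentially convertible to R0 resection following neoadjuvant therapy".

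Preoperative treatment is not reserved for tumours that need converting. Section 2.6 says "The preoperative phase will consist of 2–4 cycles of neoadjuvant SOX or XELOX chemotherapy, with or without immunotherapy", for both groups. Randomisation uses one stratification factor, which is not resectability: "This trial was stratified by neoadjuvant chemotherapy ± immunotherapy using stratified block randomization" (section 2.3). Resectability at entry is also absent from the subgroup list in section 2.9.

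The fixed testing sequence in section 2.9 covers EFS, then OS, DFS and the recurrence/metastasis rates. The surgical conversion rate is not in it.

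**The concern.** Conversion means that a tumour which could not be resected becomes resectable. The protocol's own footnote uses the idea in that sense when it speaks of tumours convertible to R0 resection. The endpoint, however, counts every R0 resection after neoadjuvant therapy, whatever the tumour's status at entry.

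Two things are at stake. The first is the level: a reader will take the reported rate as the share of unresectable tumours made resectable, when it also contains planned operations on tumours that were resectable throughout. The second is the contrast: an effect on conversion is averaged with patients in whom there was nothing to convert. Neither can be disentangled afterwards unless the baseline class has been recorded.

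**Working it through.** **Plan's own figure.** There is none to reproduce. The protocol gives no expected conversion rate, no R0 rate and no share of participants unresectable at entry. The only input taken from it is the group size: "the final target enrollment is set at 143 participants per group".

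**Reading the text.** Take a participant resectable at entry who receives the preoperative cycles and then has an R0 resection. This participant meets the entry criteria, belongs to the patients in the definition, and had R0 resection after neoadjuvant therapy. By section 2.7.2 this is a success on the surgical conversion rate, although nothing was converted.

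**Dilution.** Let s be the share technically unresectable at entry, c the R0 rate in that share, and r the R0 rate in those resectable at entry.

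- Overall R0 rate in an arm = s·c + (1 − s)·r
- Difference between arms = s·(c1 − c0) + (1 − s)·(r1 − r0)
- If the drug changes only c, the second term is zero and the difference is s·(c1 − c0).

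Assumptions, none from the protocol: c = 50% vs 70%, and r the same in both arms. The rates below use r = 90%. The power range for all participants covers r = 85 to 95% (two proportions, two-sided 0.05, 143 per arm). Power in the subset uses 143·s per arm.

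| s | Overall R0, control vs experimental | Difference | Power, all participants | Power, unresectable subset (n per arm) |
|---|---|---|---|---|
| 10% | 86% vs 88% | 2 points | 7–9% | 18% (14) |
| 20% | 82% vs 86% | 4 points | 13–18% | 34% (29) |
| 30% | 78% vs 84% | 6 points | 23–29% | 47% (43) |
| 50% | 70% vs 80% | 10 points | 47–53% | 69% (72) |
| 70% | 62% vs 76% | 14 points | 72–74% | 83% (100) |
| 100% | 50% vs 70% | 20 points | 94% | 94% (143) |

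Example, s = 20%: 0.2 × 0.50 + 0.8 × 0.90 = 0.82; 0.2 × 0.70 + 0.8 × 0.90 = 0.86; difference 0.2 × 0.20 = 0.04.

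**How far the size depends on the unknowns.** The difference is 5 points or less only if s ≤ 5/20 = 25% for a 20-point effect, s ≤ 5/10 = 50% for a 10-point effect, or s ≤ 5/30 = about 17% for a 30-point effect. The direction of the dilution follows from the definition when r does not change. Its size does not.

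The power columns are for comparison only, since the endpoint is not formally tested. Under these assumptions restriction loses participants but still gives more power at every share below 100%, because the effect is no longer averaged away.

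**The case against.** The strongest reply is that this is a condensed article and that the denominator of a descriptive secondary endpoint is usually settled in the full protocol or analysis plan. The definition says patients without stating whether all randomised, all treated or all operated are meant. That much is fair. But the line is a complete definition with a name attached, and none of those three denominators turns it into a conversion rate. A later document could do so only by departing from the wording given.

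A second reply is that R0 resection in all participants is a worthwhile perioperative outcome. It is, and it should be kept under that name.

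Several stronger readings are tempting but are not supported:

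- A reader might infer that a real conversion effect will shrink to a few points. That needs a low unresectable share and no drug effect on R0 in patients resectable at entry. The protocol states neither, and at shares of 50 to 70% a 20-point effect still shows as 10 to 14 points.
- A reader might infer that the footnote reserves conversion for technically unresectable tumours alone. It says that potentially resectable disease includes them. It does not draw two clean classes.
- A reader might predict very high reported rates in both arms. That follows from the assumed R0 rate in resectable patients, not from the protocol.
- A reader might see a bias in the lack of stratification by resectability. Chance imbalance in an unstratified baseline factor is ordinary sampling variation and does not bias a randomised comparison in expectation.

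**Conclusion.** The point holds as a mismatch between name and definition. What section 2.7.2 defines is an R0 resection rate in a mixed population, called a conversion rate. If the drug acts on R0 only through conversion, the difference between arms equals the conversion effect multiplied by the share unresectable at entry. That share is unknown, so the table in the working is an illustration and not an estimate for this trial.

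The consequence is limited. This is a descriptive secondary endpoint outside the fixed sequence, no sample size or alpha depends on it, and the EFS conclusion is unaffected. The definition should still be corrected, because the outcome is named in the Abstract and would be misread as it stands.

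**What to change.** - Define the surgical conversion rate as the number with R0 resection divided by all randomised participants classed at baseline as technically unresectable. Count those not operated as not converted.
- Record that class as an explicit yes/no baseline field. The potentially resectable category cannot stand in for it, because that category merely includes such tumours.
- For participants already enrolled (61 of 286 at submission), take the class from source notes where it is documented. Section 2.2.1 mentions multidisciplinary assessment only within the definition of potentially resectable disease, so whether every participant has such a record needs checking.
- Report R0 resection among all randomised participants as a separate outcome under its own name.

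The cost is a change of wording, one data field and some retrospective abstraction. The downside is a smaller denominator and wider intervals: about 14 to 43 participants per arm if the share is 10 to 30%. The article reports that no data analysis has been done, so the change can still be prespecified.

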#### Safety evaluation

2.7.3

Adverse events will be monitored throughout the intervention period and graded according to the National Cancer Institute Common Terminology Criteria for Adverse Events, version 5.0. Laboratory assessments (including routine blood tests, liver and kidney function) and electrocardiograms will be performed at scheduled visits. The incidence of adverse drug reactions will be calculated as the number of patients experiencing any adverse drug reactions divided by the total number of enrolled patients.

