### Statistical analysis

2.9

All analyses will be performed using SAS software (version 9.4). Efficacy analyses will be conducted on both the Full Analysis Set (intention-to-treat principle) and the Per-Protocol Set. Safety analyses will be performed on the Safety Set. Prespecified subgroup analyses based on randomization stratification factors, and multivariable adjustment will be used to minimize the influence of treatment heterogeneity. Time-to-event endpoints (EFS, DFS, OS) will be summarized using Kaplan-Meier survival curves and compared between groups using the log-rank test. The Cox proportional hazards model will be employed for multivariate analysis to adjust for potential confounding variables. All statistical tests will be two-sided, with a *p*-value < 0.05 considered statistically significant.

Subgroup analyses: To explore potential beneficiary characteristics, we will perform prespecified subgroup analyses according to baseline clinical factors (age, sex, tumor clinical stage, T stage, N stage, PD-L1 CPS, MSI/MMR status, chemotherapy regimen, immunotherapy use, baseline Karnofsky score, TCM syndrome classification, and relevant biomarker subgroups). For each subgroup, the treatment effect on EFS will be estimated, and interactions between treatment and subgroup factors will be tested using the Cox model. The model selection strategy will be forced entry of these pre-specified variables (no stepwise selection) to avoid overfitting and multiplicity issues. Proportional hazards assumption will be tested using Schoenfeld residuals. These analyses are exploratory and hypothesis-generating; no adjustment for multiple testing will be applied. This study is not powered for formal predictive model development or validation.

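### Section 2.7.3 divides adverse drug reactions by all enrolled patients, while section 2.9 puts safety analyses on the Safety Set: one rate, two denominators

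*Protocol article*

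**What the plan says.** Section 2.7.3 (Safety evaluation) gives an explicit formula. The numerator is "the number of patients experiencing any adverse drug reactions", and this count is "divided by the total number of enrolled patients".

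Section 2.9 (Statistical analysis) assigns populations to analyses. For efficacy: "Efficacy analyses will be conducted on both the Full Analysis Set (intention-to-treat principle) and the Per-Protocol Set". For safety: "Safety analyses will be performed on the Safety Set". The Safety Set is thus named separately from the intention-to-treat population. The article does not define it and does not equate it with all enrolled patients.

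Two other sections bear on who counts as enrolled. In section 2.3, site staff "performed subject assignment via the randomization system after confirming eligibility and obtaining informed consent", with no condition that a first dose has been taken. In section 2.5, "the final target enrollment is set at 143 participants per group", a figure that already includes the dropout allowance.

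**The concern.** The incidence of adverse drug reactions is a safety analysis, so both sections apply to it. An analyst who follows 2.7.3 divides by everyone enrolled. One who follows 2.9 divides by the Safety Set. Whenever some enrolled patients fall outside the Safety Set, the two can report different figures from the same data, and the article does not say which takes precedence.

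The direction matters more than the size. A patient who never takes the granules cannot react to them, yet adds one to the 2.7.3 denominator. For reactions to study drug, that formula can err only towards a lower rate. Safety is a stated aim of the trial, so its headline rate should not rest on a denominator that can only flatter it.

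**Working it through.** **What can be reproduced.** The article states no adverse drug reaction rate, so there is no such figure to recover. The one document figure used is the group size: 114 / (1 − 0.20) = 142.5, rounded up to 143, which agrees with section 2.5.

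**Inputs**
- Enrolled per arm: N = 143 (section 2.5).
- Share of enrolled patients who never take study drug: f. Not given; assumed 2%, 5% and 10%, with 0% for reference.
- Reaction rate among treated patients: p. Not given; assumed 30%, with 10% and 50% to show the range.
- The 20% in section 2.5 ("To account for an estimated 20% dropout rate") is a dropout allowance, not a never-dosed share, and is not used as f.

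**Formula.** Let x be the number of patients in an arm with a reaction to study drug, all of them treated.
- Rate on the Safety Set (usual meaning): x / [N(1 − f)] = p
- Rate by 2.7.3, applied per arm: x / N = p(1 − f)
- Understatement: p − p(1 − f) = p × f

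**Results for p = 30%**

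| f | 2.7.3 rate | Understatement |
|---|---|---|
| 0% | 0.30 × 1.00 = 30.0% | 0 points |
| 2% | 0.30 × 0.98 = 29.4% | 0.6 points |
| 5% | 0.30 × 0.95 = 28.5% | 1.5 points |
| 10% | 0.30 × 0.90 = 27.0% | 3.0 points |

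At p = 10% the understatement is 0.2, 0.5 and 1.0 points for f = 2%, 5% and 10%. At p = 50% it is 1.0, 2.5 and 5.0 points.

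**Check with whole patients, N = 143**
- f = 5%: 136 treated, 41 with a reaction. 41/136 = 30.1% against 41/143 = 28.7%.
- f = 10%: 129 treated, 39 with a reaction. 39/129 = 30.2% against 39/143 = 27.3%.

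These agree with the formula apart from rounding to whole patients.

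**If reactions to background therapy also count.** Let q be the reaction rate among patients who never take the granules but do receive chemotherapy, with or without immunotherapy. The 2.7.3 rate becomes p(1 − f) + q × f, and its shortfall against the Safety Set rate is f × (p − q). With q = 0 this is the result above. With q = p the shortfall is nil, although the two sections still name different populations.

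**Effect on the comparison between arms.** With the same f in both arms, each rate is multiplied by (1 − f). The risk ratio is then p1(1 − f) / [p2(1 − f)] = p1 / p2, unchanged. The risk difference shrinks by the factor (1 − f).

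**The case against.** The strongest reply is that the contradiction is partly inferred. The article never defines the Safety Set, and such definitions usually sit in the full protocol or SAP. Section 2.9 is the analysis section and follows convention, so 2.7.3 may simply be loose wording in a condensed article. This limits the weight of the point but does not remove it. The complaint is not that a definition is missing. It is that 2.7.3 states a formula, and that the formula names a different population from 2.9. The conflict would disappear only if the Safety Set were all enrolled patients, which nothing in the article says.

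A second reply also stands in part. Section 2.7.3 does not restrict adverse drug reactions to the granules, and every participant is also due to receive SOX or XELOX, with or without immunotherapy. Someone who skips the granules could still enter the numerator. The (1 − f) dilution therefore holds only for reactions to study drug.

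Third, f is probably small. Complications that prevent oral intake are an exclusion criterion, and eligibility is confirmed before assignment. Adverse drug reaction incidence is also neither the primary endpoint nor part of the fixed testing sequence. All of this is fair and bears on the size.

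Two stronger readings are tempting, and the article supports neither:
- A reader might infer that dividing by all 286 patients would halve each arm's rate. That needs an arm-level numerator over a trial-wide denominator. Taken literally, the sentence makes both trial-wide and gives one pooled incidence; taken per arm, it makes both arm-specific. Neither reading halves anything.
- A reader might infer that the comparison between arms is systematically biased because non-exposure differs by arm. Allocation is concealed and the products are described as identical in appearance, packaging, taste and smell. Before the first dose nothing gives participants or investigators a reason to behave differently by arm. Chance imbalance remains possible, but there is no basis for a systematic one.

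**Conclusion.** The inconsistency is real and minor. Sections 2.7.3 and 2.9 give different denominators for the same safety rate, and the article does not reconcile them. Followed as written, 2.7.3 can understate the rate of reactions to study drug by a relative amount equal to f: 0.6 to 3.0 points on an assumed 30% rate for f between 2% and 10%, and nothing if every enrolled patient takes at least one dose.

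The size rests on three assumptions that the article does not settle: that the Safety Set means participants who took study drug, that the rate is meant to describe reactions to study drug, and that f lies in the assumed range. The mismatch of wording depends on none of the numbers. It deserves correction because 2.7.3 states a rule that conflicts with 2.9, not because the effect is large.

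**What to change.** Restate 2.7.3 so that the incidence of adverse drug reactions is calculated per arm, as the number of participants with at least one adverse drug reaction divided by the number in that arm's Safety Set, in agreement with 2.9. The definition of the Safety Set can stay wherever the full protocol or SAP gives it; 2.7.3 need only refer to it.

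The cost is one sentence, with no change to data collection or sample size. The reported rate may become slightly less favourable. The trial status section says that no data analysis has been performed, so the change can be made now without any appearance of being driven by results.
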